### Statistical Analysis

SPSS software (version 26.0; IBM Corp) and R Statistical Software (version 4.4.0; R Foundation for Statistical Computing) are used for data analysis. Categorical variables are presented as frequencies and percentages. Normally distributed continuous data are expressed as mean (SD), while nonnormally distributed continuous or ordinal variables are summarized as median (IQR). Group comparisons employed *t* test or one-way ANOVA for normally distributed continuous variables, Mann-Whitney *U* test (2 groups) or Kruskal-Wallis *H* (multiple groups) test for non-normal/ordinal data, and chi-square test for categorical variables. For baseline data, a *P* value <.05 is considered statistically significant, indicating a significant difference in baseline characteristics between the group with frailty and the group without frailty. For missing data, considering the instability of missing values, this study used multiple imputation method (imputation tool: “mice” package in R Statistical Software [version 4.4.0]) to fill in the missing parts. Participants will be excluded if there are 3 or more candidate variables missing. After imputation, sensitivity analysis will be used to validate the plausibility of the Missing at Random assumption and the robustness of the imputation results. By comparing the results of multiple imputation datasets with complete case analysis (ie, removing missing data), we further validate the robustness of our main conclusions.

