Currently, unidimensional frailty assessment remains predominant in research involving people living with HIV or AIDS, while research on multidimensional frailty status is still insufficient, and the factors leading to multidimensional frailty in hospitalized older adults living with HIV or AIDS are not yet clear. Therefore, we will explore multidimensional frailty as the main outcome. The theory of unpleasant symptoms (TOUS), as a mid-level theory, is commonly used to establish methodological methods and analyze results, or as a theoretical framework for analyzing influencing factors [13,14]. The theory suggests that factors that affect symptoms can be divided into 3 parts: physiological, psychological, and environmental. The three interact and influence each other, jointly affecting disease symptoms and influencing the outcome of symptoms. Guided by TOUS, we categorized potential frailty factors in hospitalized older adults living with HIV or AIDS into physiological, psychological, and environmental domains based on literature review and clinical practice. Ultimately, all included potential influencing factors were identified and finalized through online expert consultation.

Early-stage frailty in older adults living with HIV or AIDS is often relatively insidious. However, to our knowledge, there is relatively little research and development in China on frailty prediction tools for hospitalized population. To address these gaps, we aim to develop and validate a prediction model using 3 machine learning algorithms. By comparing their performance, we seek to enhance risk prediction accuracy, ultimately improving patient prognosis and health outcomes.

This prospective observational study aims to (1) determine the prevalence of multidimensional frailty among hospitalized people living with HIV or AIDS aged ≥50 years, (2) identify factors associated with frailty guided by the TOUS, and (3) develop and validate risk prediction models.

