### Prediction Variables

#### Determination of Candidate Variables

The selection of predictive variables for this prediction model is based on a review of literature and consensus opinions by an expert group, taking into account its practicality in clinical settings. Possible clinically relevant variables will be selected as candidate predictors of frailty and evaluated after the patient’s admission examination is completed. Through 3 group discussions and 1 online expert consultation meeting, a total of 31 candidate predictor variables were identified and classified into physiological, psychological, and environmental factors based on TOUS. The variables to be explored are detailed in the following subsections.

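### Dropping participants with three or more missing candidate variables defeats the planned imputation, can distort prevalence, and is invisible to the planned sensitivity check

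*Protocol article*

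**What the plan says.** All the missing-data text stands in one paragraph of the Statistical Analysis section of the protocol article.

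- Imputation: "this study used multiple imputation method", with the mice package in R.
- Exclusion: "Participants will be excluded if there are 3 or more candidate variables missing". No rationale is given, and no analysis is exempted.
- Missing at random: "sensitivity analysis will be used to validate the plausibility of the Missing at Random assumption and the robustness of the imputation results". The method of this analysis is not named.
- Complete cases: "By comparing the results of multiple imputation datasets with complete case analysis (ie, removing missing data"), with the stated purpose that "we further validate the robustness of our main conclusions".

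Two other places matter. The Introduction gives as its first aim to "determine the prevalence of multidimensional frailty among hospitalized people living with HIV or AIDS aged ≥50 years". Determination of Candidate Variables says that "a total of 31 candidate predictor variables were identified". Under Definition of Outcomes, frailty status comes from the Tilburg Frailty Indicator alone (5 or more of 15 items), so no candidate predictor is needed to classify a participant.

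**The concern.** Multiple imputation is used so that participants with incomplete predictors can stay in the analysis. The rule removes those with the most to impute, including someone with 28 of 31 candidates observed and a known outcome.

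Missing values may also cluster. Under Data Acquisition, HIV load, CD4 count, albumin and CRP are all taken from the hospital test records. A participant without those admission results lacks four candidates and is over the limit at once. Neurocognitive testing takes place at 48 to 72 hours, so an early discharge loses it. Being untested may be related to frailty, which is the outcome.

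Three things are at stake:

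- the denominator of the prevalence estimate;
- the case mix on which the model is built;
- the reassurance a reader would take from the sensitivity analyses, which cannot see the people the rule removed.

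**Working it through.** **The plan's own figure.** The plan gives no missingness rate. The only related figure is the minimum sample size, and it reproduces: n = 10 / [(0.9 − 1) × ln(1 − 0.1483/0.9)] = 555.4, rounded up to 556. Events are 556 × 0.593 = 330, or 33 per parameter.

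**Share excluded.** Inputs: 31 candidates (Determination of Candidate Variables), threshold 3 (Statistical Analysis), 603 recruited (Results). The rate q per variable and independence between variables are assumptions.

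P(excluded) = 1 − P(0) − P(1) − P(2) for a Binomial(31, q). At q = 3%: 1 − 0.389 − 0.373 − 0.173 = 0.065.

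| q per variable | Excluded | Of 603 | Complete cases |
|---|---|---|---|
| 1% | 0.4% | 2 | 73.2% |
| 2% | 2.4% | 14 | 53.5% |
| 3% | 6.5% | 39 | 38.9% |
| 5% | 20.1% | 121 | 20.4% |

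With 28 variables in place of 31, the excluded shares are 0.3%, 1.8%, 5.1% and 16.3%. Clustering breaks the independence assumption: if a share c of participants lacks all four laboratory values, at least c is excluded whatever the other rates.

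**Effect on prevalence.** Let p = 0.593 (Sample Size), and let ef and en be the assumed shares of frail and non-frail participants excluded.

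Reported prevalence = p(1 − ef) / [p(1 − ef) + (1 − p)(1 − en)]

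- ef = en = 5%: 59.3%, no bias.
- ef = 10%, en = 5%: 0.5337 / (0.5337 + 0.3867) = 58.0%, a shift of −1.3 points.
- ef = 20%, en = 5%: 55.1%, −4.2 points.
- ef = 30%, en = 10%: 53.1%, −6.2 points.

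**Effect of dropping incomplete participants on a model.** A simulation with N = 400,000 used y ~ Bernoulli(0.593), x2 ~ N(0.4y, 1) and x1 ~ N(0.6y + 0.3·x2, 1), with x1 sometimes missing. It used five imputations of x1 from y and x2. The full-data logistic fit was intercept 0.118, x1 0.602, x2 0.220, with prevalence 59.4%.

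- Missing completely at random: complete cases gave no material bias in prevalence or coefficients.
- Missingness depending on x2 only: complete-case slopes were right, but prevalence fell to 57.8%.
- Missingness depending on y and x2: in complete cases, prevalence was 54.5%, the intercept −0.033 and the x2 slope 0.148. Imputation gave 0.115 and 0.219 for the two coefficients.

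**What the comparison can show.** The same simulation gave two further cases.

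- Not at random, logit P(missing) = −2.3 + 0.5y + 0.8·x1·y: the x1 slope was 0.447 in complete cases and 0.448 after imputation, against a truth of 0.602. The methods agreed and both were wrong. They did differ on the intercept (0.023 and 0.203) and the x2 slope (0.217 and 0.272).
- At random, logit P(missing) = −2.2 + 0.5y + 0.8·x2·y: the x2 slope was 0.068 in complete cases and 0.219 after imputation, against 0.220. The methods disagreed although imputation was right.

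Agreement therefore does not support missing at random, and disagreement does not refute it. Separately, a participant with three or more missing candidates is removed from the imputed data by the rule and from the complete-case data by definition. Neither side of the comparison contains that person.

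**The case against.** The strongest reply is that little may be missing. Inclusion requires the ability to cooperate with investigations and testing. Blood sampling is part of the routine admission work-up, and staff complete and verify questionnaires for those who cannot do so themselves. The text does not say that the four laboratory values come from a single draw. At 1% missing per variable the rule costs about two people in 603. This stands, and it limits the size of the point. It gives no reason for having the rule.

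A shift of 1.3 points is also small beside sampling error. With 10% and 5% excluded, about 555 of 603 remain, and the 95% margin is 1.96 × √(0.58 × 0.42 / 555) = ±4.1 points. That is fair, but a selection bias is not part of the confidence interval and does not shrink with more recruitment.

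The rule sits among text on imputing predictors and may not have been meant to govern prevalence. That may be so, but it is worded for participants and the denominator for the first aim is not stated. Clarification is the least that is needed.

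A reader might infer that the plan tests missing at random by comparing imputed with complete-case results. The text does not say this. It assigns missing at random to a sensitivity analysis whose method is not named, and gives the complete-case comparison a separate purpose, robustness of the conclusions. An article may leave that method to a fuller document, so its absence is not held against the plan. What remains is that no analysis of observed data can *validate* the assumption.

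**Conclusion.** The point holds as a risk, not as a demonstrated bias. As worded, the rule discards known outcomes from the prevalence estimate and usable participants from the model, for no stated benefit, and the planned comparison cannot reveal its effect.

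The size cannot be fixed from the document. Under independent missingness of 1% to 5% per variable the loss runs from 0.4% to 20%. The prevalence shift is zero if exclusion is unrelated to frailty, and −1.3 points if 10% of frail and 5% of non-frail participants are excluded. All these rates are assumptions.

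Two stronger readings are tempting:

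- That the rule does bias prevalence and the model. The document gives no missingness rates, and in the simulation slopes survived when missingness depended only on an observed predictor.
- That the rule would exclude everyone, because IL-6, sTNFR1 and sTNFR2 are listed among the laboratory indicators but were not collected. That depends on one possible count of the 31, and the Discussion says these markers are not in the analysis. It is worth stating which variables the limit counts, but no more follows.

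The change should be made now, since the Results section says no data analysis has been conducted.

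**What to change.** 1. **Prevalence.** State that it is estimated in all participants with a Tilburg score, whatever predictors are missing.
2. **Model.** Remove the count-based exclusion and impute missing candidates for all participants with an observed outcome. Keep the three-or-more exclusion only as a sensitivity analysis, name the variables it counts, and tabulate excluded against retained participants, including frailty status.
3. **Missing at random.** Replace the claim to validate its plausibility with *assess sensitivity to departures from missing at random*, using a delta-adjusted analysis in mice over a stated range of shifts. Keep the complete-case results as a descriptive comparison.

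The cost is a change of wording, one extra sensitivity run, and somewhat more reliance on the imputation model for participants with many missing values. The retained sensitivity analysis in item 2 shows how much that reliance matters.

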### Model Development and Validation

The sample size of this study is relatively small. This study uses logistic regression (LR) as the benchmark for performance comparison. LR has certain advantages in handling limited sample sizes and can demonstrate feature coefficients and significance levels. Although random forest (RF) has the risk of overfitting in small sample situations, it has certain advantages in handling complex nonlinear relationships. We will minimize the risk by adjusting decision tree parameters and cross-validation. Support vector machine (SVM) is particularly suitable for handling situations with high feature dimensions but relatively small sample sizes, and its regularization properties help control the risk of overfitting. As one of the tree ensemble algorithms, XGBoost also has the risk of overfitting and relatively complex parameter tuning. Neural networks have high requirements for sample size and poor clinical interpretability for small sample studies. We hope to ensure the robustness of the model to a large extent in this small sample study. For future larger-scale research, more complex machine learning methods will be used.

Randomly split the training set and validation set in a 7:3 ratio, and use the following machine learning algorithms for modeling: LR model, RF, and SVM. Univariate analysis combined with least absolute shrinkage and selection operator regression will be used to screen predictive factors. To address nonlinearity, we will analyze the relationships between relevant factors and HIV frailty risk using restricted cubic splines and incorporate them as spline terms in the model. Restricted cubic splines can also indirectly capture potential interactions between features. Interactions and complex nonlinear decision boundaries will be handled by selecting nonlinear kernel functions in SVM. The primary model performance evaluation metric is accuracy, which represents the proportion of correctly predicted samples in classification tasks. This will be considered alongside precision, recall, *F*_1_-score, and area under the receiver operating characteristic curve for comprehensive assessment. Through integrated comparison, the algorithm achieving optimal balance across these metrics will be selected as the final model for predicting frailty status in people with HIV.

To prevent overfitting, the nonlinear modeling effects of all models will be validated via cross-validation. A 3×10-fold cross-validation scheme will be adopted, with each split performed independently, yielding 30 model performance estimates (eg, area under the curve [AUC], *F*_1_-score). Overfitting will be monitored by ensuring that the performance difference between the training set and the cross-validation set remains below a threshold (AUC difference <0.05). During cross-validation, hyperparameters (including max_depth for RF, and C and γ for SVM) will be jointly optimized to select the parameter combination that achieves the best trade-off between fitting efficacy and generalization ability, thereby further reducing overfitting risk. The final model selected through cross-validation will then be evaluated on an independent test set for ultimate performance assessment. For internal validation, we performed bootstrap resampling (n=1000 iterations) to generate training sets matching the original cohort size. Retraining prediction models with these training sets and evaluating performance using the above indicators, we will repeat this process to obtain internal validation performance. External validation will be implemented in prospective observational studies, using external period validation to analyze samples from September 1, 2025 to December 31, 2025. In future research, we plan to collaborate with other institutions to continue external validation. The sample size required for external validation in this study is 1/4 of the modeling sample size, and the minimum sample size for external validation is calculated to be 139 cases (Figure 1).

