### Sample Size

Frailty occurrence in people living with HIV or AIDS represents a binary outcome. Previous studies reported a frailty incidence of 59.3% in hospitalized older adults living with HIV or AIDS, which was assessed using the FRIDE frailty scale [16]. Due to the current lack of a frailty prediction model for HIV/AIDS patients, it is not possible to determine *R*^2^ through previous models. Based on the proportion of outcome events, the maximum *R*^2^ (*R*^2^ cs_max) is calculated to be 0.7416. Assuming that the new model can explain 20% of the variability, the expected *R*^2^ is 0.1483 (=0.7416×20%). We expect the predictive model to include 5 to 10 predictor variables, based on “pmsampsize(type=‘b’, csrsquared=0.1483, parameters=10 , prevalence=0.593).” In this formula, csrsquared represents the ability of the expected prediction model to explain outcome variability; parameters represent the total number of candidate variables expected to be included; and prevalence refers to the prevalence of frailty events in older people living with HIV or AIDS in China based on previous research. The calculation indicates that a minimum sample size of 556 is required. A total of 330 events were expected, corresponding to 33 events per predictor variable. The above results are calculated using the pmsampsize package in R Statistical Software (version 4.4.0) [17].

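### If significance levels computed on the same data that selected the factors are used to identify factors associated with frailty, they do not carry their nominal error rate

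*Protocol article*

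**What the plan says.** The Introduction of the Protocol article gives three aims. The second is to "identify factors associated with frailty guided by the TOUS". Under Determination of Candidate Variables, "a total of 31 candidate predictor variables were identified".

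Model Development and Validation then sets the route: "Univariate analysis combined with least absolute shrinkage and selection operator regression will be used to screen predictive factors". Logistic regression is the benchmark among three algorithms, and one reason given is that "LR has certain advantages in handling limited sample sizes and can demonstrate feature coefficients and significance levels". The same section says: "Randomly split the training set and validation set in a 7:3 ratio".

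The only stated threshold is in Statistical Analysis: "For baseline data, a *P* value <.05 is considered statistically significant". It concerns the comparison of frail with non-frail patients. The article gives neither a univariate entry level nor a LASSO penalty rule.

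Cross-validation, the 1000 bootstrap resamples, the test set and the temporal validation are all described for model performance. None is described as protecting inference on coefficients. The Discussion refers to the effects of identified risk factors and hopes that they will help staff give preventive care.

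**The concern.** An ordinary Wald p-value in logistic regression assumes that the terms were fixed before the outcome was examined. Here a term enters only because it is associated with frailty in these same patients. A factor with no independent association reaches the final model largely because its sample association happened to be large, or because it is correlated with a real predictor. In the first case its refitted p-value is biased towards significance, and its interval lies too far from the null.

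The article describes no other multivariable route to the second aim, so the natural reading is that the selected logistic model will supply the factor list. At stake is whether readers can take p<.05 for a listed factor at face value. The predictive performance of the models is a separate matter and is not challenged here.

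**Working it through.** **Inputs from the article.** 31 candidates; prevalence 0.593, expected R² 0.1483 and 10 parameters ("csrsquared=0.1483, parameters=10 , prevalence=0.593", Sample Size); total 556; 7:3 split, so 0.7 × 556 = 389 for training and 167 held out. Patient Recruitment gives 445 and 111 instead; results at 389, 445 and 556 were similar.

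**Assumptions.** Univariate entry at p<.05; final tests at two-sided .05; number of true predictors; correlation among candidates.

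**The plan's own figure.** "The calculation indicates that a minimum sample size of 556 is required". With shrinkage S = 0.9, n = P / [(S − 1) ln(1 − R²/S)] = 10 / [(−0.1) × ln(1 − 0.1483/0.9)] = 10 / 0.01801 = 555.4, so 556. It reproduces. The article states no error rate for selected factors.

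**Simulation.** Each of 100-150 runs per setting applied univariate t tests at p<.05, then LASSO with 10-fold cross-validation, then a logistic refit with Wald tests on the same data. A null factor is a candidate with zero coefficient in the true model.

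Share of surviving null factors with p<.05:
- Nulls uncorrelated with every true predictor, 5 or 8 true predictors: 56-67%.
- No true predictor at all: 86-100%.
- Local correlation 0.3 (n = 389): 19-35%. Local correlation 0.5: 10-23%.
- All pairs equally correlated (n = 389-556): 5-25% at 0.1, 10-15% at 0.3, 9-11% at 0.5.
- LASSO without the univariate screen, uncorrelated nulls: 15-17% with 8 true predictors, 47-58% with none.

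A separate simulation with the univariate screen and refit but no LASSO gave 60-88% with independent candidates, and about 6-21% with serial correlation 0.3-0.5 and six true factors.

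**Rate per null candidate.** This is (nulls kept per run × share significant) / number of nulls, after univariate screen and LASSO at the minimum-error penalty:
- n = 556, uncorrelated, 8 true: 1.20 × 0.650 / 23 = 3.4%.
- n = 556, all pairs 0.3, 8 true: 6.19 × 0.100 / 23 = 2.7%.
- n = 556, no true predictor: 1.63 × 0.859 / 31 = 4.5%.
- n = 389, uncorrelated, 5 true: 1.25 × 0.561 / 26 = 2.7%.

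The unselected 31-candidate model gave 5-7%.

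**At least one false factor per analysis.** Screen plus refit without LASSO: about 40-80%. With LASSO added: about 24-58% when true predictors exist, and up to 79% when none do.

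**Share of declared factors that are false, six true and 25 null.** At n = 389 the route had 91% power, so 0.91 × 6 = 5.46 true factors are declared. A false share of 12.6% then means 0.126 / 0.874 × 5.46 = 0.79 false factors, or 0.79 / 25 = 3.1% per null, in line with the rates above. At correlation 0.5 and n = 556, with 89% power and 1.8% per null, the share is 0.45 / (5.34 + 0.45) = 7.8%. Hence about 8-13%.

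**Remedy.** With a training set of 389 and 5 or 8 true predictors, testing the same selected factors in the held-out 30% gave 3-7% for null factors.

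Monte Carlo error is roughly 1-5 percentage points.

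**The case against.** The strongest reply has four parts.

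1. **The article does not say that post-LASSO p-values will answer the second aim.** The quoted sentence explains the choice of a performance benchmark. The only p<.05 rule is for baseline comparisons, no confidence intervals for coefficients are announced, and the final model may be a random forest or support vector machine. This stands in part: the use is inferred. It remains the natural reading, because no other multivariable analysis of factors is described and significance levels are named as a merit.

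2. **A reader might infer that chance factors are called significant 50-90% of the time instead of 5%.** The documents do not support that. The high figures need null factors uncorrelated with every true predictor. Many candidates here are plainly related: height, weight and BMI; a nutrition scale containing BMI and weight; anxiety and depression. For correlated nulls the range is about 5-35%. The comparison also sets a rate conditional on surviving a screen against a rate per candidate tested. A claim of at least three times nominal in every case fails too.

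3. **A reader might infer that screening produces more false factors than testing everything.** It does not. With 31 independent unselected tests at 5% and no true predictor, the chance of at least one false positive is 1 − 0.95^31 = 80%, at or above what the screened route gives. Part of the problem is ordinary multiplicity in an exploratory aim.

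4. **Harm is limited.** The Discussion says that the cross-sectional design cannot establish causation and expresses only a hope about preventive care. This stands, and it bears on severity.

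**Conclusion.** The point holds in a limited form. The article sets out outcome-driven selection followed by logistic regression valued for its significance levels, with no stated protection for coefficient inference. If those p-values and intervals serve the second aim, a surviving factor's p<.05 does not mean what it says. How far it departs depends on a correlation structure that nobody knows in advance: from about nominal up to 35% for nulls correlated with true predictors, and about 55-90% or more for uncorrelated nulls.

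The number of false factors is not inflated per candidate. The weakness is that the reported p-values cannot reliably separate the false factors from the real ones on the list. All sizes rest on the assumed entry level, the assumed numbers of true factors and the assumed correlations.

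**What to change.** 1. Report the selected model's coefficients as prediction weights, without p-values or wording that calls a factor significant or independent.

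2. For the second aim, refit the selected factors in patients not used for selection, and quote odds ratios, intervals and p-values from that fit. The planned 30% validation set or the temporal validation sample can serve. State that univariate screening and LASSO are confined to the training patients; otherwise the held-out set is not independent of selection.

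3. Optionally, add a prespecified logistic model with all non-redundant candidates (not height, weight and BMI together) and multiplicity control, as a supporting analysis. Its feasibility is fair: 330 expected events over 31 candidates is about 10.6 per candidate if each takes one parameter, and fewer with multi-category factors or splines.

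**Cost.** Analysis wording and a little code; no new data. The article says that no analysis has yet been done. Intervals widen by about √(389/167) = 1.5 times with 167 held-out patients, or √(389/139) = 1.7 times with the stated minimum of 139 temporal cases, so fewer factors may be declared significant. The optional model with Benjamini-Hochberg control can also lose power: in simulation at equal n = 556 it fell from 98% to 95% with independent candidates and from 89% to 71% at correlation 0.5.

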**Methods:**

This study is an ongoing single-center prospective observational study, with a plan to recruit at least 556 hospitalized older adults living with HIV or AIDS (n=445 for development and n=111 for validation). According to the theory of unpleasant symptoms, candidate predictors are categorized into physiological factors (including sociodemographic factors, disease-related influencing factors, sleep, nutrition, and neurocognitive function), psychological factors (including anxiety and depression status), and environmental factors (including social support status). Potential predictors are screened using univariate analysis and least absolute shrinkage and selection operator regression to identify variables for final model inclusion. Model construction and validation employ 3 standard machine learning algorithms: logistic regression, random forest, and support vector machine. Model performance will be evaluated by reporting accuracy, precision, sensitivity, specificity, and the area under the curve.

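### Univariate screening can drop masked or non-monotone predictors before they reach LASSO or a spline, and single-variable splines do not capture interactions

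*Protocol article*

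**What the plan says.** The Abstract (Methods) states: "Potential predictors are screened using univariate analysis and least absolute shrinkage and selection operator regression to identify variables for final model inclusion". Model Development and Validation repeats the step: "Univariate analysis combined with least absolute shrinkage and selection operator regression will be used to screen predictive factors". Neither place gives the order of the two steps or the cut-off for passing the univariate one.

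The univariate tests are described only under Statistical Analysis. They are the t test or ANOVA for normal data, then a Mann-Whitney or Kruskal-Wallis "test for non-normal/ordinal data, and chi-square test for categorical variables". The same section says, with reference to baseline data, that a P "value <.05 is considered statistically significant, indicating a significant difference in baseline characteristics between the group with frailty and the group without frailty".

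After the screening sentence, the plan says it will examine the relation of relevant factors to frailty risk "using restricted cubic splines and incorporate them as spline terms in the model". No spline-based screen, and no spline basis inside LASSO, is described. Two sentences on interactions follow: "Restricted cubic splines can also indirectly capture potential interactions between features" and "Interactions and complex nonlinear decision boundaries will be handled by selecting nonlinear kernel functions in SVM".

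**The concern.** The plan wants to model nonlinearity, but the tests it describes for choosing variables cannot see every kind of nonlinearity. A t test or Mann-Whitney test asks whether frail patients have a higher or lower value than non-frail patients. If risk rises at both ends of a predictor's range, the two groups can have nearly the same mean and rank, and the predictor fails before any spline is fitted. A test of one variable alone also cannot see a predictor whose effect is hidden by a correlated candidate with an opposing effect.

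Two aims are at stake. The second study objective is to identify factors associated with frailty, and there are 31 candidates. If one screened list feeds all three algorithms, as the Abstract suggests, random forest and the support vector machine cannot recover what was dropped.

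The interaction sentence is a separate error. A restricted cubic spline is a function of one variable, so a logistic model built from such terms remains additive unless product or tensor terms are added. None is mentioned.

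**Working it through.** **Inputs.** No stated figure bears directly on this point. The documents supply the sample sizes and the prevalence:

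- The planned total is 556. It reproduces as 10 / (0.1 × −ln(1 − 0.1483/0.9)) = 556, with the shrinkage target of 0.9 assumed.
- The 7:3 split gives 0.7 × 556 = 389 for training. The stated development set is 445.
- The prevalence is 0.593, so the intercept is ln(0.593/0.407) = 0.38.

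Effect sizes and the standard normal predictor are assumptions, because the documents give none. The 0.05 level is taken from the baseline comparisons.

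**Non-monotone predictor.** Take logit = a + c·x². For a distribution symmetric about its centre, x and x² are uncorrelated, so the groups do not differ in mean or rank. The odds ratio at ±2 SD against the centre is exp(4c): 3.3 for c = 0.3, 4.1 for c = 0.35 and 7.4 for c = 0.5. The spline test is a likelihood-ratio test of a 4-knot restricted cubic spline (3 df).

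Share of runs in which the predictor is retained at n = 389 (400 runs per row):

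| Shape | t test | Mann-Whitney | Spline test |
|---|---|---|---|
| Centred U, c = 0.5 | 2.5% | 3.0% | 99.5% |
| Centred U, c = 0.35 | 4.75% | 4.75% | 92.5% |
| U, vertex 0.5 SD off centre (c = 0.5) | 90% | 93% | 100% |
| U, vertex 1 SD off centre (c = 0.5) | 100% | 100% | 100% |
| Monotone, saturating | 98% | 98% | 98% |
| Monotone, threshold | 56% | 54% | 66% |
| Linear, 0.3 per SD | 82% | 78% | 70% |

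A larger sample does not help. At n = 556 the t and Mann-Whitney tests still retain the centred U shapes only 3 to 4% of the time, against 99 to 100% for the spline test.

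For the weaker c = 0.3, separate sets of 600 runs gave 4 to 6% for the t and Mann-Whitney tests. The spline test gave 84 to 85% at n = 389 and 92 to 93% at n = 445. A further repeat gave 4 to 8% against 86 to 100%. With 400 runs, the Monte Carlo standard error around 5% is √(0.05 × 0.95/400) = 1.1 percentage points, so these rates amount to the nominal false-positive rate.

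**Masked predictor.** Take two predictors correlated 0.6, with log-odds of +0.8 and −0.48 per SD. Seen alone, the second has a net effect of about −0.48 + 0.6 × 0.8 = 0. At n = 389 it passes the t test in 3 to 4% of runs, while a joint logistic model detects it in 95 to 97%. This is exact cancellation, the worst case; partial masking would cost less.

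**Interaction.** Take logit = a + 0.8·x₁·x₂, n = 389, 150 runs, with AUC measured in new data:

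| Correlation of x₁ and x₂ | Additive splines | Product term |
|---|---|---|
| 0 | 0.50 | 0.67 |
| 0.3 | 0.55 | 0.66 |
| 0.7 | 0.64 | 0.67 |

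With independent predictors, additive splines capture nothing. With strongly correlated predictors they partly mimic the interaction.

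**The case against.** Much can be said for the plan.

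- **Breadth of the loss.** A reader might infer that the screen removes nonlinear predictors in general. The table refutes that: saturating and off-centre U shapes nearly all pass, and the threshold shape loses only about 10 percentage points against the spline test. For a linear effect the spline test is the weaker one (70% against 82%).
- **Relevance here.** Nothing in the documents says that any candidate is U-shaped. The sleep, nutrition, cognition, anxiety and depression, and social support scales run from better to worse, so a monotone relation is the natural expectation. Many other candidates are categorical, where splines do not apply. Masking can still affect any of them. Some candidates clearly overlap (BMI with the nutrition score that contains it, anxiety with depression), but the documents do not show that any is in fact masked.
- **Screening rule.** A reader might take P<.05 as the entry rule and univariate-then-LASSO as the sequence. Neither is stated. The threshold is given for baseline comparisons, and the full plan may specify another rule.
- **Interactions.** A reader might infer that the plan depends on splines for interactions. It does not: the next sentence assigns them to the nonlinear kernel, and random forest is fitted too. The algorithms are compared on performance metrics, which do not depend on the mistaken sentence.
- **Overfitting.** It would be wrong to say that overfitting is ignored. Cross-validation, an AUC-gap threshold, bootstrap retraining, a test set and temporal validation are all described.
- **The cause.** LASSO on linear terms is also blind to a centred U, so removing the univariate screen alone would not cure that part.

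These points narrow the concern. They do not remove it, because the Abstract makes univariate analysis part of selection and the tests described have these two blind spots under any cut-off near 5%.

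**Conclusion.** The point holds in a limited form. On any reading in which a failed univariate test excludes a variable, two kinds of real predictor are kept at about the false-positive rate (roughly 3 to 8% in these simulations): those masked by a correlated candidate, and non-monotone ones with little net shift. A joint model would keep the first kind and a spline-based selection the second, in most runs. Other nonlinear predictors mostly pass. The size rests on assumed effects and on two worst-case shapes; how many of the 31 candidates are affected cannot be known from the documents.

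The spline-interaction sentence is wrong as written for a logistic model with single-variable spline terms. Its consequence is confined to how the logistic benchmark is described and interpreted.

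**What to change.** 1. Keep the univariate comparisons as a descriptive table and state that they exclude no variable.
2. Let LASSO select from all prespecified candidates.
3. Name in advance the few continuous candidates for which a non-monotone relation is plausible. Give these a spline basis at the selection step, kept or dropped as a group, instead of adding splines only to variables already selected. Leave the rest linear, since the spline test loses power for linear effects.
4. Delete the sentence that restricted cubic splines capture interactions. State that the logistic model is additive unless product terms are prespecified, and that interactions are modelled by random forest and the nonlinear SVM kernel.

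**Cost.** Somewhat more analysis work is needed, and the spline terms use parameters: a 4-knot spline takes 3 where a linear term takes 1. The sample size was calculated for 10 parameters while 31 candidates are listed, so the spline list should be short. Dropping the univariate screen does not itself add candidates, because the screen already looks at all of them. The Results section reports that no data analysis has been done, so the change can still be made in advance.
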